# Descriptive Factors

- 1. Dose level as assigned by Registration Office: -1 vs. dose level 0 vs. dose level 1 vs. expansion

# Treatment/Follow–up Decision at Evaluation of Patient

- 1. Continuation of therapy

Patients who have not had disease progression and have experienced acceptable toxicity are to continue treatment per protocol until confirmed PD, unacceptable toxicity or refusal. And then they will go to event monitoring where patient and disease status will be reported every 6 months until death or a maximum of 5 years post-registration.

- 1. Progressive disease

The first instance in which a patient’s disease status meets the RECIST criteria for PD will continue two additional cycles of treatment per protocol and then undergo disease revaluation. If the initial documented progression is not confirmed by this scan, patients will continue treatment per protocol. If the initial documented progression is confirmed by this scan, patients will go to the event-monitoring phase where patient and disease status will be reported every 6 months until death or a maximum of 5 years post- registration. ***Exception: Patients who develop PD in the CNS should discontinue study treatment and go to Event Monitoring.***

- 1. For those on treatment at least one year and in complete response (CR)

At investigator’s discretion patients who have completed at least one year of protocol therapy and have had a complete response (CR) may discontinue all protocol therapy when the duration of the complete response has been at least 6 months (that is, at least 3 consecutive scans showing CR).

- 1. Discontinuation of protocol therapy

Criteria for discontinuation of protocol therapy include:

- - - Disease progression: Where disease progression is: the development of a new metastatic lesion or an objective status of disease progression (as defined by RECIST criteria) on two consecutive evaluations at least 6 weeks apart (section 13.2). ***Exception: Patients who develop PD in the CNS should discontinue study treatment.***
    - Request by patient to discontinue study treatment
    - Unacceptable toxicity
    - Intercurrent illness that would, in the judgment of the investigator, affect assessments of clinical status to a significant degree or require discontinuation of drug
    - Administration of radiotherapy, non-protocol chemotherapy, immunotherapy, biological agents, or an experimental drug during the trial
    - Development of new primary cancer
    - Ineligibility

Patients who discontinue treatment due to progression or development of a second primary, desire for non-protocol treatment, intolerability, patient request, physician decision, or inter-current illness preventing further administration of protocol treatment will proceed to event monitoring phase of the trial where patient and disease status until death or a maximum of 5 years post-registration

- 1. Ineligible

A patient is deemed ineligible if after registration, it is determined that at the time of registration, the patient did not satisfy each and every eligibility criteria for study entry.

- - - If the patient received any protocol treatment, patient should discontinue study treatment and all data (except biospecimens) up until the point of discontinuation must be submitted. Patients will proceed to event monitoring phase of the trial where patient and disease status will be reported every 6 months until death or a maximum of 5 years post-registration.
    - If the patient never received any protocol treatment, on-study material (except biospecimens) and the End of Active Treatment/Cancel Notification Form must be submitted. No further No further data submission is necessary.
  1. Cancel

A patient who withdraws consent before any study treatment is given. On-study material (except biospecimens) and the End of Active Treatment/Cancel Notification Form must be submitted. No further data submission is necessary.

- 1. Treatment after PD

Subsequent treatment after confirmed PD is at the discretion of their attending physician.

- 1. PD in CNS

Patients who develop PD in the CNS only should discontinue study treatment and proceed to event monitoring phase of the trial where patient and disease status will be reported every 6 months until death or a maximum of 5 years post-registration.

MC1577 50 MCCC Amendment 8

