# Test Schedule

| Treatment Cycle | Pre- registration | ≤14 days prior to  regist- ration | Active Monitoring Phase | | | | | |
| --- | --- | --- | --- | --- | --- | --- | --- | --- |
|  |  |  | Cycles 1-4^1^ | | | | Day 1 Subsequent cycles [21- day cycle] | At confirmed disease progression^2^ |
| Tests and procedures |  |  | C1D8 (±1  day) | C2D1 (±3  days) | C3D1 (±3  days) | C4D1 (±3  days) | (± 3 days) |  |
| HLA Class I Typing^R^ |  | X |  |  |  |  |  |  |
| ECOG performance status |  | X | X | X | X | X | X | X |
| History, physical exam, vital signs^3^, and weight |  | X | X | X | X | X | X | X |
| Child Pugh Score |  | X |  | X | X | X | X | X |
| Height |  | X |  |  |  |  |  |  |
| Adverse event assessment |  | X | X | X | X | X | X | X |
| Urine Pregnancy test |  | X4 |  |  |  |  |  |  |
| CBC with Differential:^5^ |  | X6 | X | X | X | X | X | X |
| Chemistry group: AST, ALT,  Bilirubin (total and direct), Creatinine, albumin, INR, LDH |  | X6 | X | X | X | X | X | X |
| TSH |  | X7 |  |  | X |  | X7 | X |
| Tumor imaging and measurement ^,8^ |  | X8 |  |  |  |  | X9 | X |
| Research blood specimens (see Section 14.0)^10,R^ |  | X | X | X | X | X | X10 | X |
| Tissue specimens (see Section 17.0)^,R^ | X11 |  |  |  |  |  | X12 | X12 |
| BRAF V600E and V600K  mutation testing |  | X |  |  |  |  |  |  |

- - 1. Cycle 1= 28 day, Subsequent Cycles=21 days.
    2. Confirmed progression is an objective status of progression on two consecutive evaluations at least 6 weeks apart.
    3. Vital signs must include blood pressure and heart rate.
    4. For women of childbearing potential only. Must be done ≤7 days prior to registration.
    5. CBC differential must include hemoglobin, platelets, absolute neutrophil count, absolute lymphocyte count, and absolute monocyte count
    6. CBC with differential and chemistry groups must be done ≤14 days prior to registration.
    7. TSH testing is to be performed ≤14 days prior to registration. And at the end of each even numbered cycle ( 2, 4, 6, 8, 10, etc.) until confirmed progression. If TSH is abnormal, T3 and free T4 testing should be performed.
    8. The initial tumor imaging (either CT or MRI, with preference for CT) will be performed ≤28 days prior to registration. The same imaging technique will be used in a patient throughout the study. If an excisional biopsy of a target lesion is to be done, baseline tumor imaging must be performed after the biopsy is done.

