    9. Imaging is to be performed at the end of Cycle 4, 6, 8, 10, and 12. If a patient has not had a confirmed disease progression after Cycle 12, subsequent scans will take place at the end of every 3^rd^ cycle of treatment thereafter (that is, at the end of Cycle 15, 18, 21 until confirmed disease progression). See Section 11.
    10. Mandatory research blood specimen will be collected at Cycle 1 Day 8 and at the beginning of each cycle for Cycles 2-4, then at the beginning of every cycle when tumor imaging is performed until confirmed progression or at treatment discontinuation if not for PD.
    11. Mandatory core needle biopsy. A newly obtained tumor biopsy is required, unless tissue is

available for research use from a prior biopsy obtained ≤90 days prior to registration.

- - 1. Mandatory tissue/biopsy is required at the time of the first disease assessment (the evaluation at the end of Cycle 4). Optional tissue/biopsy will be obtained at the time of confirmed progression. Prior to and following biopsy hold ibrutinib per section 8.4.

R Research funded (see Section 19.0)

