# Protocol Treatment

- 1. Treatment Schedule

Use actual weight or estimated dry weight if fluid retention Cycle 1 treatment = 28 days

All subsequent treatment cycles = 21 days (±3 days)

| Drug | Dose | Treatment | Retreatment |
| --- | --- | --- | --- |
| Ibrutinib | assigned at registration | PO daily (Day 1 to 28  of Cycle 1, then Day 1- 21* on subsequent cycles) | Every 21 days  (±3 days)  until confirmed progression |
| Pembrolizumab | 200 mg | IV injection on Day 8 of Cycle 1 and then Day 1 of each  subsequent cycle | Every 21 days (±3 days) until confirmed progression |

* Patients should receive a sufficient quantity of ibrutinib to last until the next scheduled treatment visit.

- 1. Determination of Maximum Tolerated Dose (MTD)
  2. Dose Escalation Scheme

| Dose level | Ibrutinib** |
| --- | --- |
| -1 | 140 mg |
| 0* | 280 mg |
| 1 | 420 mg |

* Starting dose level

** If the patient has clinical or laboratory evidence of liver failure during the treatment, then calculate the Child-Pugh score and adjust the ibrutinib dose (see Table 8.3).

NOTE: Doses will not be escalated in any individual patient.

- 1. MTD Determined

As of MCCC Amendment 6, the MTD has been determined to be Dose Level 1. Dose Level 1 will be used for the expansion cohort.

- 1. Dose Limiting Toxicities

Dose limiting toxicities (DLT) are defined to be:

| ***Toxicity*** | ***DLT Definition*** |
| --- | --- |
| Hematologic | Grade 4 ANC, Grade 4 Hgb, or PLT <25,000 |
| Renal | Serum creatinine ≥2 times baseline |
| Neurologic | ≥Grade 2 neurosensory or neuromotor toxicity |
| Other nonhematologic | ≥Grade 3 per NCI Common Terminology Criteria for Adverse Events (CTCAE) version 4.0* |

*Grade 3 rash or fever despite maximal supportive treatment(s) will be considered dose-limiting; all grade 4 rash and fever will be considered a DLT.

The maximum tolerated dose is defined as the highest dose level among those tested where at most one out of 6 patients develops a DLT prior to the start of their second cycle of treatment and the next highest dose level is such that 2 out of a maximum of 6 patients treated at this dose level developed a DLT prior to the start of their second cycle of treatment.

- 1. Dose escalation plan

NOTE: As of MCCC Amendment 6, the MTD has been determined to be Dose Level 1. A minimum of 2 or a maximum of 6 patients will be accrued to a given dose level.

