# Treatment Evaluation Using RECIST Guideline

- 1. Requirements

The first scan after treatment initiation will be performed at the completion of Cycle 4 and will be then performed at the complete of every other cycle of treatment until disease progression is confirmed or 12 cycles of treatment have been administered without a confirmed disease progression (that is, imaging is to be done at the end of Cycles 4, 6, 8, 10, and 12). If a patient has not had disease progression after Cycle 12, subsequent scans will take place at the end of every 3^rd^ cycle of treatment thereafter (that is, at the end of Cycle 15, 18, 21 until confirmed disease progression)

Disease progression for this protocol is defined as meeting the RECIST criteria for disease progression on two consecutive evaluations at least 6 weeks apart.

- 1. Definitions of Measurable and Non-Measurable Disease
  2. Measurable Disease
  3. A non-nodal lesion is considered measurable if its longest diameter can be accurately measured as ≥1.0 cm with CT scan, CT component of a PET/CT, or MRI.
  4. A malignant lymph node is considered measurable if its short axis is

>1.5 cm when assessed by CT scan (CT scan slice thickness recommended to be no greater than 5 mm).

**NOTE:** *Tumor lesions in a previously irradiated area are not considered measurable disease.*

- 1. Non-Measurable Disease

All other lesions (or sites of disease) are considered non-measurable disease, including pathological nodes (those with a short axis ≥1.0 to <1.5 cm). Bone lesions, leptomeningeal disease, ascites, pleural/pericardial effusions, lymphangitis cutis/pulmonis, inflammatory breast disease, and abdominal masses (not followed by CT or MRI), are considered as non-measurable as well.

**NOTE:** ‘Cystic lesions’ thought to represent cystic metastases can be considered as measurable lesions, if they meet the definition of measurability described above. However, if non-cystic lesions are present in the same patient, these are preferred for selection as target lesions.

Lymph nodes that have a short axis <1.0 cm are considered non- pathological (i.e., normal) and should not be recorded or followed.

- 1. Guidelines for Evaluation of Measurable Disease
  2. Measurement Methods:
- All measurements should be recorded in metric notation (i.e., decimal fractions of centimeters) using a ruler or calipers.

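### Section 13.3 explains 6 months of complete response as 3 consecutive CR scans, but three scheduled scans span only 12 to 18 weeks, so the two thresholds disagree for CR first seen at Cycle 10 or later

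*Protocol*

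**What the plan says.** Protocol Section 13.3 (patients on treatment at least one year and in CR) is a permissive stopping rule, used at the investigator's discretion. It applies to "patients who have completed at least one year of protocol therapy" who have had a CR, and it requires the CR to have lasted "at least 6 months (that is, at least 3 consecutive scans showing CR").

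The calendar behind the scan count is set elsewhere:

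- Cycle length (Section 4, Test Schedule, footnote 1): "Cycle 1= 28 day, Subsequent Cycles=21 days". Section 7.1 adds a window: "All subsequent treatment cycles = 21 days (±3 days").
- Imaging to Cycle 12 (Section 4, footnote 9): "Imaging is to be performed at the end of Cycle 4, 6, 8, 10, and 12". Section 11.1 agrees: "imaging is to be done at the end of Cycles 4, 6, 8, 10, and 12".
- Imaging after Cycle 12 (Section 11.1): every third cycle, "at the end of Cycle 15, 18, 21 until confirmed disease progression".
- Extra scan (Section 11, Measurement at Follow-up Evaluation): a further scan is mandatory 6 weeks after CR or PR is first documented.

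**The concern.** 'That is' offers the scan count as the meaning of 6 months. An investigator may fairly take three CR scans in a row as proof that the duration has been met, and a scan count is easier to tick off than a duration. If three scans cover much less than 6 months, the sentence carries two thresholds that disagree.

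At stake is when a complete responder may stop both drugs. A patient managed by the scan count could stop after a shorter CR than one managed by the duration, with fewer pembrolizumab doses, although both were handled under the same sentence.

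**Working it through.** **Inputs.** Cycle 1 is 28 days and later cycles 21 days (Sections 4 and 7.1). Scans fall at the end of Cycles 4, 6, 8, 10 and 12, then every third cycle (Sections 4 and 11.1). The minimum time on therapy is one year (Section 13.3). Assumption: 6 months is 26 weeks and one year is 52 weeks.

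**Scan weeks.** End of Cycle n = 4 + 3(n − 1) weeks.

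- Cycles 4, 6, 8, 10, 12: weeks 13, 19, 25, 31, 37.
- Cycles 15, 18, 21, 24: weeks 46, 55, 64, 73.
- Cycle 17 ends at 4 + 3 × 16 = week 52, the one-year floor.

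**The stated equivalence.** Span of three consecutive scheduled scans = third scan week − first scan week.

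- First CR at Cycle 4, 6 or 8: 25 − 13 = 31 − 19 = 37 − 25 = 12 weeks.
- First CR at Cycle 10: 46 − 31 = 15 weeks.
- First CR at Cycle 12 or later: 55 − 37 = 64 − 46 = 18 weeks.

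None reaches 26. On scheduled scans, spanning 26 weeks takes 6 scans from Cycle 4, 5 scans from Cycle 6, 8 or 10, and 4 scans from Cycle 12 or later.

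**Consequence if the scan count is treated as sufficient (scheduled scans only).** Earliest stop by scan count = max(52, third CR scan). Earliest stop by duration = max(52, first CR + 26). Shortfall = 26 − (stop by scan count − first CR), or zero if negative.

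| First CR | Week | Stop by scan count | CR at that stop | Stop by duration | Shortfall |
|---|---|---|---|---|---|
| Cycle 4 | 13 | 52 | 39 weeks | 52 | none |
| Cycle 6 | 19 | 52 | 33 weeks | 52 | none |
| Cycle 8 | 25 | 52 | 27 weeks | 52 | none |
| Cycle 10 | 31 | 52 | 21 weeks | 57 | 5 weeks |
| Cycle 12 | 37 | 55 | 18 weeks | 63 | 8 weeks |
| Cycle 15 | 46 | 64 | 18 weeks | 72 | 8 weeks |

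Cycles after 15 repeat the last row. For Cycle 10, if the decision waits for the Cycle 18 scan at week 55, the CR has lasted 55 − 31 = 24 weeks and the shortfall is 2.

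**Doses.** Pembrolizumab is given as "IV injection on Day 8 of Cycle 1 and then Day 1 of each" subsequent cycle. The doses falling between the two stops are at weeks 52 and 55 for Cycle 10 (2 doses), weeks 55, 58 and 61 for Cycle 12 (3), and weeks 64, 67 and 70 for Cycle 15 (3).

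**If the mandatory 6-week scan counts as one of the three.** For first CR at Cycle 4 to 10 it coincides with the next scheduled scan, so nothing changes. Later it falls between scheduled scans:

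- Cycle 12: scans at weeks 37, 43 and 46. The one-year floor moves the stop to week 52, after 15 weeks of CR: 11 short.
- Cycle 15 or later: scans at weeks 46, 52 and 55. Stop at week 55, after 9 weeks of CR: 17 short.

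**Can delays rescue the equivalence?** With every cycle 3 days late, the spans are 12 + 4 × 3/7 = 13.7, 15 + 5 × 3/7 = 17.1 and 18 + 6 × 3/7 = 20.6 weeks. A maximal treatment hold under Section 8.2 (12 weeks after the last dose instead of 3) adds 9 weeks, so an 18-week span could reach 27. That holds only if scans move with the cycles, which the protocol does not state.

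**The case against.** The strongest reply is that the 6-month clause is complete and measurable by itself, and that 'at least 3' sets a minimum that can sit beside a longer duration. On that reading nobody stops early. This stands as a limit on the harm, but it does not make the equivalence true: on the nominal schedule a 26-week CR already contains 3 to 5 scheduled scans, so the parenthesis is either wrong or idle.

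A second reply is that the stable-disease bullet in Section 11 gives a 12-week interval after Cycle 12, and two such gaps make 24 weeks, close to 6 months. That may be where the gloss came from, but the documents do not say so. It is still about 2 weeks short, and it conflicts with the every-third-cycle imaging in Sections 4 and 11.1.

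A third reply is that the consequence is small. That is accepted: the rule is discretionary and the one-year floor removes the early complete responders.

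A reader might infer something stronger, that Section 13.3 lets complete responders stop after only 12 weeks of CR. The documents do not support this. The 12-week spans belong to CR first seen at Cycle 4, 6 or 8, and by week 52 those patients have 39, 33 or 27 weeks of CR.

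**Conclusion.** The stated equivalence is wrong on the protocol's own calendar: three scheduled scans cover 12, 15 or 18 weeks, not about 26. It matters only if the scan count is treated as sufficient, and then only for CR first seen at Cycle 10 or later. The shortfall is about 5 weeks at Cycle 10 (about 2 if the decision waits for Cycle 18) and about 8 weeks from Cycle 12 on scheduled scans. It is about 11 weeks (Cycle 12) or 17 weeks (Cycle 15 or later) if the mandatory 6-week scan counts. These figures rest on nominal cycle lengths and 26 weeks for 6 months.

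A reader might also infer that the slip disturbs the efficacy analysis. It does not: Section 16.6 defines tumor response by CR or PR on two consecutive evaluations at least 8 weeks apart, without using the Section 13.3 rule, and the MTD and sample size are unaffected. The protocol gives no CR rate, so the number of patients touched, within a maximum enrollment of 23, cannot be estimated. This is a minor wording correction.

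**What to change.** In Section 13.3, replace 'that is' with 'and' and drop the parentheses, so that both conditions must hold: a CR of 6 months or more, and three or more consecutive CR scans. The duration then governs on the nominal schedule.

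Deleting the parenthesis would also remove the false equivalence, but it would lose the scan minimum when it is most useful. If a scheduled scan after Cycle 12 is missed, or scans slip with a long hold, a 26-week CR could rest on only two scheduled scans.

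The cost is one phrase, with no change to imaging, sample size or endpoints. The downside falls on late complete responders who would have stopped on the scan count. They wait about 5 to 8 weeks longer (2 or 3 more pembrolizumab doses), or 9 to 12 weeks if the site waits for the next scheduled scan after 6 months: week 64 instead of 52 for Cycle 10, 64 instead of 55 for Cycle 12, and 73 instead of 64 for Cycle 15. Where the mandatory 6-week scan would have counted, the wait to reach 6 months is about 11 weeks (Cycle 12) or 17 weeks (Cycle 15 or later). On the nominal schedule patients with first CR at Cycle 4, 6 or 8 are not delayed.

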**Note:** Non-target lesions and non-target lymph nodes should be evaluated at each assessment, especially in the case of first response or confirmation of response. In selected circumstances, certain non-target organs may be evaluated less frequently. For example, bone scans may need to be repeated only when complete response is identified in target disease or when progression in bone is suspected.

11.432 Evaluation of Target Lesions

Complete Response (CR): All of the following must be true:

1. Disappearance of all target lesions.
2. Each target lymph node must have reduction in short axis to <1.0 cm.

Partial Response (PR): At least a 30% decrease in PBSD (sum of

the longest diameter for all target lesions plus the sum of the short axis of all the target lymph nodes at current evaluation) taking as reference the BSD (*see* Section 11.41).

Progression (PD): At least one of the following must be

true:

1. At least one new malignant lesion, which also includes any lymph node that was normal at baseline (<1.0 cm short axis) and increased to ≥1.0 cm short axis during follow-up.
2. At least a 20% increase in PBSD (sum of the longest diameter for all target lesions plus the sum of the short axis of all the target lymph nodes at current evaluation) taking as reference the MSD (Section 11.41). In addition, the PBSD must also demonstrate an absolute increase of at least 0.5 cm from the MSD.
3. See Section 11.32 for details in regards to the requirements for PD via FDG-PET imaging.

Stable Disease (SD): Neither sufficient shrinkage to qualify for

PR, nor sufficient increase to qualify for PD taking as reference the MSD.

11.433 Evaluation of Non-Target Lesions & Non-target Lymph Nodes Complete Response (CR): All of the following must be true:

1. Disappearance of all non-target

lesions.

1. Each non-target lymph node must have a reduction in short axis to

<1.0 cm.

Non-CR/Non-PD: Persistence of one or more non-target

lesions or non-target lymph nodes.

Progression (PD): At least one of the following must be

true:

1. At least one new malignant lesion, which also includes any lymph node that was normal at baseline

(<1.0 cm short axis) and increased to ≥1.0 cm short axis during follow- up.

1. Unequivocal progression of existing non-target lesions and non-target lymph nodes. (NOTE: Unequivocal progression should not normally trump target lesion and target lymph node status. It must be representative of overall disease status change.)

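### Section 13.4, as worded, stops treatment at a first new metastatic lesion, while Section 13.2 continues a first non-CNS RECIST progression, new lesions included, until it is confirmed

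*Protocol*

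**What the plan says.** Section 13.4 (discontinuation of protocol therapy) lists disease progression first and spells it out as "the development of a new metastatic lesion or an objective status of disease progression (as defined by RECIST criteria) on two consecutive evaluations", at least six weeks apart. It then points to 13.2 and adds that PD in the CNS stops study treatment.

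Section 13.2 (progressive disease) says that a patient whose disease first meets RECIST PD "will continue two additional cycles of treatment per protocol and then undergo disease revaluation". It goes on: "If the initial documented progression is not confirmed by this scan, patients will continue treatment per protocol". Only a confirmed progression sends the patient to event monitoring. The one stated exception is PD in the CNS.

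Section 11.432 lists among the sufficient conditions for PD: "At least one new malignant lesion, which also includes any lymph node that was normal at baseline". Section 11.433 repeats this for non-target disease, and the overall-status table in 11.44 gives PD whenever there is a new site of disease.

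The other governing statements all rest on confirmation:
- Section 11.1: "Disease progression for this protocol is defined as meeting the RECIST criteria for disease progression on two consecutive evaluations at least 6 weeks apart".
- Test schedule, footnote 2: "Confirmed progression is an objective status of progression on two consecutive evaluations at least 6 weeks apart".
- Section 13.1: patients without progression and with acceptable toxicity are to "continue treatment per protocol until confirmed PD, unacceptable toxicity or refusal".
- The Section 7 treatment table continues both drugs until confirmed progression, and the schema uses the same trigger.

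**The concern.** The two sections that tell a site what to do at progression give different instructions for one common-sense case: a first new lesion outside the CNS. Section 13.4 sets the new lesion as its own limb, joined by an or to a second limb that carries the two-evaluation condition. Section 13.2 treats the same finding as a first RECIST PD that must be confirmed.

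This reaches the analysis as well as patient handling. Section 16.6 classifies best tumor response during treatment and includes a category for confirmed PD. It measures PFS to the documentation of disease progression without saying which definition of progression is meant. If some patients are stopped at the first new lesion and others continue to a repeat scan, they do not have the same opportunity to have PD confirmed, to have it overturned, or to respond later on treatment.

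**Working it through.** The plan states no figure to reproduce. The check is a comparison of the sections and one interval.

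1. **Is a new lesion RECIST PD here?** Yes. One new malignant lesion suffices under 11.432 and 11.433, and the 11.44 table makes the overall status PD. A first new lesion is therefore a first RECIST PD in the sense of 13.2.

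2. **Does 13.2 exempt it?** Only if it is in the CNS. For CNS progression 13.2 and 13.4 both stop treatment, so there is no conflict there. The conflict is confined to new lesions outside the CNS.

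3. **Is the difference merely one of interval?** No. Cycles after the first last 21 days, so two further cycles are 2 × 21 = 42 days = 6 weeks. That nominally matches the six-week minimum in 13.4, 11.1 and footnote 2. The disagreement lies in the new-lesion limb.

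4. **Worked case.** A patient has stable target lesions and one new non-CNS metastasis on the scan at the end of Cycle 4.
   - End of Cycle 4: 28 + 3 × 21 = day 91. Overall status is PD by the 11.44 table.
   - Under 13.2 the patient is treated through Cycles 5 and 6 and rescanned at 28 + 5 × 21 = day 133. Treatment stops only if PD is confirmed.
   - Under 13.4 as worded, treatment stops at day 91.
   - Difference: 133 − 91 = 42 days of treatment, and one on-treatment scan.

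5. **The two readings of 13.4.**
   - *Condition attached to the second limb only:* a new lesion stops treatment at once. This contradicts 13.2 and has no counterpart in 11.1, 13.1, the treatment table or footnote 2.
   - *Condition attached to both limbs:* the conflict goes, but the new-lesion limb then adds nothing, because RECIST PD on two evaluations already includes new lesions.

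6. **What follows for a patient stopped at the first new lesion.**
   - Progression is met under 13.4 but not under 11.1, which needs two evaluations.
   - There may be no confirming scan, since event monitoring is a status report every 6 months.
   - Best response during treatment cannot be confirmed PD, and no later response during treatment can be seen.
   - Footnote 10 of the test schedule collects the closing research blood sample at confirmed progression, or at discontinuation for a reason other than PD. This patient fits neither trigger.

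**The case against.** The strongest reply is that the conflict is a drafting leftover with a clear intended meaning. The 13.4 bullet cites 13.2. Its CNS exception also makes most sense if non-CNS lesions need confirmation: if every new lesion stopped treatment at once, the exception would matter only for growth of previously treated brain metastases. The schema, treatment table, test schedule, 11.1 and 13.1 all point to confirmation. This is good evidence of intent, and it makes the shared-condition reading tenable. It does not cure the wording. That reading leaves a redundant limb, and a site that gives each word effect stops the patient. A stopping rule should not need this much inference.

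The reply is also right to limit what follows. A reader might infer that every first progression is caught between the two rules; CNS progression is not. A reader might infer that the ±3-day cycle windows allow a gap shorter than 42 days; the requirement of at least six weeks between evaluations rules that out for a confirmed PD. A reader might infer that 13.4 shifts the PFS curve by six weeks. Whether progression is dated at the first or the confirming scan is a separate question, and it would remain if the new-lesion limb were deleted.

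**Conclusion.** The point holds as an internal inconsistency in a stopping rule, limited to first new lesions outside the CNS. For each such patient the two sections differ by two cycles, nominally 42 days of treatment, and by whether PD can be confirmed or overturned on treatment. This rests on the text alone.

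The number of patients affected cannot be derived: the protocol does not give the share of first progressions that are new lesions. Nor do the documents show that the expansion cohort's result would change. The tumor-response endpoint, judged against two responses in 14 patients, would be affected only if a patient with a first new lesion went on to a response meeting the two-evaluation criterion in 16.6, and nothing in the protocol says how often that happens. PFS is secondary, and 16.6 describes all results as exploratory. The case for correction is that the rule decides who stays on treatment and what is recorded as progression, and that the correction is small.

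**What to change.** Reconcile 13.4 with 13.2, 11.1 and footnote 2 of the test schedule so that one stated rule governs new lesions outside the CNS. Which rule applies is for the investigators to decide.

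In 16.6, state that the progression event used for PFS and for best response follows that same definition. Where confirmation is required, a first PD that the repeat scan does not confirm should not count as an event. Simply dating PFS at the first PD scan under either route would not do, because it would count progressions that 13.2 later treats as unconfirmed.

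The cost is one clause in 13.4 and one or two sentences in 16.6, with no change to sample size or visit schedule if the confirmation rule is the one retained. If the investigators choose the other rule, 11.1, 13.1, 13.2, the treatment table, the schema and footnotes 2 and 10 need matching edits.
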